### Experimental procedure

#### Study flow

The onset of the Stop-X program, as a part of (where applicable) the pre-operative and/or the postoperative follow-up treatment, is individualized: a graduated, shared and criteria-based decision is underlying [10]. The participants must be released for the training components by their treating orthopedic specialist and by their physiotherapists. Likewise, the athletes, themselves, must indicate their physiological readiness. It is aimed to commence the Stop-X program at a time 4 to 8 months post surgery (Fig. 1).

**Fig. 1 Fig1:**
[figure not shown]
Standard Protocol Items: Recommendations for Interventional Trials (SPIRIT) flowchart: Schedule of enrollment, interventions and assessments

The end of the (scheduled) intervention is the unrestricted RTS decision (aimed at 12–18 months post surgery). After this time point, the participants may continue the intervention but no further functional assessments will be conducted. Before (where applicable) surgery and until the unrestricted RTS decision, but at least until 12 months post surgery, all outcomes are assessed once a month. Thus, each participant is measured at least five times to a maximum of 12 times. Twelve (12), 18 and 24 months post reconstruction, follow-up measurements and recurrence monitoring follow. For this purpose, all participants are contacted by means of a structured telephone interview (separate consent). Participants are then asked for potential subsequent ACL re-injuries and other complaints/injuries. All measurements, except the structured telephone interviews, are performed by self-administration. The measures consist of jump landing tasks (10 min duration) and a questionnaire battery (5 min duration). The DJST is followed by the functional secondary outcomes. The latter consists of quality assessments during simple (combined) balance side and front hops, as well as quantity (centimeters) assessments of single-leg hops for distance. All hop/jump tests are self-administered, filmed from the frontal view (3-m distance) using the participant’s own smartphone. Videos are than expert-rated using the blinded videos. This setup has been shown to be valid when compared to 3D motion-capture systems for the analyses of sagittal-plane knee angles [15]. All videos are transferred using a safe big content transfer (PowerFolder Enterprise File Sync und Share; Düsseldorf; Germany). To assure blind assessment, only the participants’ pseudonym is used.

Secondary patient-reported outcomes are assessed questionnaire-based: knee function, kinesiophobia, RTS after ACL injury and training/therapy volume (frequency – intensity – type and time). All questionnaires are completed online at www.surveymonkey.de using the participant’s pseudonym.

Both the training and measurements are instructed and supervized by means of (online) control of training, outcome assessment adherence and correct execution.

#### Primary outcome – Drop Jump Screening Test

The DJST is a common RTS criteria with a predictive value on an ACL rupture [8, 16]. Following warm-up exercises, patients take a bipedal hip-width stance on a box with a 32-cm target height. A bipedal drop jump follows: frontal step – drop – reactive jump with the shortest possible ground contact time. The knee position is rated at three pre-defined points during this drop-jump cycle: (1) initial ground contact at the end of the drop from the box, (2) lowest point of the body’s center of gravity at the jump’s reversal point and (3) ground take-off when the feet leave the surface for the reactive vertical jump. At each of these points, the distance between (a), the hip joints and (b), the centres of the patella of the two knees are measured. The percentage of the knee distance in comparison to the hip distance was calculated to calculate the normalized knee distance. Knee-separation and hip distance is analyzed using the video-analysis software Kinovea (France). Three jumps are performed, the middle one to be further analyzed. This measurement setup and the subsequent analyses are highly inter-rater reliable (κ = .92; 95% confidence interval (CI) 0.829–0.969) and moderately intra-rater reliable (κ = .55; 95% CI 0.49–0.61) [17], respectively. In the same validation study, a sensitivity of 63% and a specificity of 83% for the classification of “high-risk” participants (index group identified by expert observers) of the DJST was found.

#### Secondary outcomes: quality and quantity of the functional hop and jump tests

For sagittal-plane jumping-quality rating, the single Balanced Front Hop Test [18] was chosen. Participants have to hop over a square on the floor with a 40 × 40-cm edge length with hands on their hips; the end position after landing must be kept for at least three continuous seconds. The frontal-plane jumping-quality rating is undertaken using the Balanced Side Hop Test [18]; the participants hop over laterally (to the direction of the test foot (right or left) ) the same square and, immediately after landing, a reactive hop back to the starting position is initiated. After each trial, the participants have, again, to maintain the controlled landing position for three consecutive seconds with their hands on their hips [18].

Three hops for each condition and leg (randomized order) are performed, the middle one for each condition and leg to be further analyzed. Quality rating criteria are (1) feet remain stable on the ground after landing, (2) knees remains in the sagittal plane during all movements and (3) the trunk remains in the sagittal plane during all movements [18].

The single-leg hop for distance (SLHD) assesses (the quantity of) dynamic balance and single-leg-jumping performance ability. The participants stand on one leg with the toes behind the rear line of the square. They then hop as far as possible and have to land in a controlled manner. The whole hop must be performed one-legged. Three successful hops per leg (randomized order) are performed; each leg’s best trial (in centimeters) is selected for further analysis. The measurement properties for the SLHD are excellent, reliability is ICC = 0.97 (CI 0.9–0.99) and the standard error of measurement is 3.5% [19]. It is considered valid in terms (as a major part of a testing battery) of predicting a subsequent ACL injury [4, 5].

#### Secondary outcomes: self-reported data

All questionnaires will be used in their validated German translation.

The Return-to-Sport after ACL injury (RSI-ACL) questionnaire assesses a participants’ fear of loading their reconstructed knee during their main sporting activity. Ten 11-point Likert-scale questions are used, a total score value of > 56 indicates sufficient confidence for RTS [20]. The sum score assessment is highly reliable (Cronbach’s alpha = 0.92) [21] and valid [22].

Further (self-reported) control variables to be used will be the Tegner and Lysholm score, International Knee Documentation Committee knee evaluation form (IKDC-2000), Knee injury and Osteoarthritis Outcome Score (KOOS), subscale activities of all daily living (ADL), injury history, demographics, pain, and task-specific fear of movement/re-injury (visual analog scale (VAS) 10 cm) and kinesiophobia (Tampa Scale of Kinesiophobia; TSK).

The Tegner and Lysholm score [23] contains a 0–10-point Likert scale to assess a participant’s activity level, scaled from low-level daily living activity to high-level competitive sports level. Scoring is from 0 = low-level activity regarding knee loading, up to and including 10 = highest possible level of activity regarding knee loading. The Lysholm knee scoring scale rates symptoms and function during ADLs using eight scales to build a 0–100-point sum score. Test-retest reliability was found to be sufficient [22]. The IKDC-2000 uses 18 items across three subdomains to assess: symptoms, sports activities and function. Differently graded Likert scales are used. Test-retest reliability is high, whereas the internal consistency and cross-cultural validity are unknown [22]. The KOOS subscale ADL is one of five KOOS subdomains and must be scored from 0 to 4. Test-retest reliability was found to be high [22]. The TSK uses 11 items across the domain “fear of movement/(re-)injury”; it is scored using 4-point Likert scales. Internal consistency and structural validity were found to be sufficient [22].

By means of a structured telephone interview, the time/date of the consensus, evidence-based, shared, positive return-to-play decision and potential re-injuries/complications/adverse effects are inquired. Further, the participants will be asked on their individual implementation capacity (barriers and chances) using a non-structured survey.

### Intervention

The training interventions (in particular the Stop-X arm) consist of self-administered home-based exercises which are step-wise graduated and follow wound-healing and functional restoration criteria. The training frequency for both arms is scheduled to be three times per week. A duration of 30 min is aimed for each session. The program follows current (secondary) prevention guidelines [24–26]. The program (in German) can be found online (pdf): http://deutsche-kniegesellschaft.de/wp-content/uploads/2017/02/DKG_Stop-X_Prävention-von-Sportverletzungen-am-Kniegelenk.pdf (permanent link, status 10/5/18) and (video description): https://stop-x.de/(permanent link, status 10/5/18). Details on the two training schemes (Stop-X versus Classic) are displayed in Table 1. All aspects of the training are divided into the wound-healing phases and the therapy goal. All similarities of and differences between the Classic and Stop-X exercise regimens are displayed.

**Table 1 Tab1:** Therapy/intervention regimen for both study arms. Standard/Classic rehabilitation strategies were conducted according to grade-A guidelines [27, 28]. The secondary preventive Stop-X program follows the recommendations in [24–26]

Wound-healing phase and/or time post surgery	Therapy goal	Classic	Stop-X
Inflammation phase	Reduction of inflammation	Brace: range of motion restriction 0–0-90° at 20-kg partial knee load	
		Manual therapeutic, passive closed kinematic chain mobilization; hip and ankle integrated	
		Measures against post-operative swelling and temperature increase, home-based measures for auto-mobilization (under compression)	
		Trunk and scapula control; non-affected-side static motor control, i.e., single-leg stance	
Proliferation phase Approximately weeks 3–12 post reconstruction	Pain reduction and mobilization [27, 29]	Knee-joint mobilization in restricted range of movement, patellar mobilization	
		Stretching: Mm. ischiocruales, M. gastrocnemius, M. iliopsoas, M. tractusiliotibialis	
		Motor control of trunk and scapula; non-affected-side static motor control, i.e., single-leg stance	
Approximately after week 7 post reconstruction		Brace: range of motion unrestricted	
		Onset of motor-control training	
		Open kinetic (dorsal only) chain	
Approximately after week 10 post reconstruction		Corrective exercise with the aim to prepare for return to sport (RTS) level I	
		Single-leg dynamic-stabilizing/motor-control exercises	
		Eccentric knee mobilization open frontal kinetic chain	
Remodeling phase Level I function: Approximately after week 13 post reconstruction	Functional enhancement and recurrence prevention	Closed and open kinetic chain (ventral and dorsal)	Based on functional criteria, not time based. Information, risk assessment, correction of risky movement characteristics; teaching of basic preventive strategies; total program at/after RTS clearance Running exercises/agility exercises Straight on running, hip external rotation, change of direction runs Running with sagittal plane distance and vertical-jump components. Self-perturbed balance exercises Single-leg stance with (individually and combined) ball bouncing/unstable surface/passing a ball Jumping exercises/plyometrics vertical and distance Strengthening exercises Russian hamstrings Dynamic and side planks with/without heel raising Hip abduction One-legged squats
		Strength endurance training for (in particular) the ischiocrural muscles	
		Dynamic-stabilizing motor-control exercises, including jump landings on unstable surfaces	
Level II function: Approximately months 4–6 post reconstruction		Dynamic-stabilizing motor-control exercises, including single (affected) leg jump landings on unstable surfaces	
		Onset of impact exercises	
Level III function: Approximately after month 7 post reconstruction		Dynamic exercises (frontal plane)	
		Side-cutting maneuvers	
Level IV function: Not before 10th month post reconstruction		Dynamic multi-directional stabilization	

All participants receive detailed information on the intervention scheduled. Classic intervention participants receive a standard follow-up scheme with defined key points; the Stop-X participants receive the same Classic intervention scheme and, additionally, the detailed information in terms of information material and specific instructions (print material and links) for the Stop-X program. All participants discuss their program with the therapy team (physiotherapists, athletic trainer).

### Therapy monitoring

To monitor home-training accuracy and compliance, all patients fill in an exercise log during the home-based training (online). Frequency, intensity, type and time of the exercises are reported in a standardized procedure. Likewise, all functional/exercise measures beyond the scheduled training are reported. Using the 14-step Likert scale of Borg rates of perceived exhaustion (6 = extremely light intensity; 20 = extremely vigorous), the intensity of the exercises is further rated.

### Statistical analysis

Following range plausibility control based on potentially reachable physiological values, a visual control for non-plausible outliers will be performed. Afterwards, all analyses will be performed based on the underlying assumptions for parametric, or rather, non-parametric testing. In detail, for all difference testing, data and variance distribution (i.e., normality) are checked; for all correlation analyses, residuals, auto correlation, and heteroscedasticity, are checked. The alpha-error threshold is set at 5%, all *p* values below are considered significant.

The analyses for the primary outcome, DJST, are done confirmatory, alpha-error corrections (Bonferroni-Holm for paired and Sidak-Holm for unpaired analyses) are performed for multiple used samples and post-hoc analyses following significant omnibus testing, whilst the alpha-error remains unadjusted for the exploratory (secondary) analyses.

The main statistics are performed twice (two different data structures): once on a time-based and once on a functional-based data structure. All repeated measures statistics are thus first performed for the time-based data structure where statistics are performed on all outcomes assessed at the same real-time after reconstruction. Secondly, functional-based data-structure analyses are performed, where the first (baseline) measurement is the first “real” measurement at the time of being cleared for the assessment (varying times of 4–8 months post reconstruction). For each of the analyses on the two datasets, gain-score analyses are performed for differences from pre (baseline) to post (each following time point) of all outcomes using repeated-measures analyses of co-variance (rmANCOVAs) with potential confounders as co-variates (baseline values, injury history, sex, type and amount of sport, age, co-morbidities). In case of a systematic impact of confounders on statistics, z-transformed values are calculated and used for further analyses. Afterwards, survival analyses by means of Kaplan-Meier plotting plus between group-difference analyses using log-rank tests are performed. Hazard ratio estimations will be calculated. Events will be: (1) Time point of unrestricted RTS decision, (2) Time point of functional criterion RTS succeeded (> 60% normalized knee-separation distance at DJST) and (3) Time point of revision surgery, re-injury or subsequent injury.

All statistical analyses are performed using SPSS (SPSS Inc., IBM, Chicago, IL, USA) and BiAS (BiAS for Windows, Frankfurt, Germany).

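### The confirmatory DJST analysis has no upper time limit, but after month 12 the DJST is taken only in participants not yet returned to sport, so later between-arm comparisons are selected (fully in the time-based structure, partially from visit 6 in the function-based one)

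*Protocol article*

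**What the plan says.** All places are in the protocol article.

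- **Analysis.** Under Statistical analysis, "The analyses for the primary outcome, DJST, are done confirmatory". The main analysis is a repeated-measures ANCOVA, run once on a time-based and once on a function-based data structure. In each, "gain-score analyses are performed for differences from pre (baseline) to post (each following time point) of all outcomes". The model is fitted "with potential confounders as co-variates (baseline values, injury history, sex" and further items; RTS status is not on the list. No last time point is given.
- **Schedule.** Under Study flow (text after Fig. 1), "until the unrestricted RTS decision, but at least until 12 months post surgery, all outcomes are assessed once a month". The RTS decision, which is the planned end of the intervention, is expected between months 12 and 18. On what happens once it has been made, the article says: "After this time point, the participants may continue the intervention but no further functional assessments will be conducted".
- **Number and start of measurements.** In the same section, "each participant is measured at least five times to a maximum of 12 times", and "It is aimed to commence the Stop-X program at a time 4 to 8 months post surgery".
- **Later follow-up.** The contacts at 12, 18 and 24 months are structured telephone interviews about re-injuries and complaints. They supply no DJST values.

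**The concern.** Two stated rules do not fit together. One stops DJST measurement at the RTS decision once month 12 has passed. The other analyses DJST gains at all time points after baseline. Followed as written, the later between-arm comparisons condition on an event that happens after randomisation.

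That event is plausibly related to the outcome. The Background regards avoidance of dynamic valgus as important for a positive RTS decision, the primary outcome section describes the DJST as a usual RTS criterion, and the survival analysis uses more than 60% on the DJST as its functional RTS criterion. The event may also be related to the arm, because time to RTS is named in the null hypothesis and is a log-rank endpoint.

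Two errors are possible:

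- If Stop-X improves knee control and so speeds RTS, its better participants leave the comparison first and a real DJST benefit looks smaller.
- If Stop-X speeds RTS by another route, such as confidence, a DJST disadvantage can appear where none exists.

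A late null or reversed result could then be read as the benefit fading. The log-rank analysis captures earlier RTS but does not repair the DJST comparison.

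**Working it through.** **1. The plan's own figure.** Inputs from Sample size determination: d = 0.3, SD 14.2, two-sided alpha 5%, beta 50%. An exact two-sample t-test gives power 0.499 at 86 and 0.503 at 87 per group, so 87 reproduces. 87/0.7 = 124.3, hence 125 per group and 250 in total. The target effect is 0.3 × 14.2 = 4.26 points.

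**2. Which visits are affected.** With clearance in month c, visit k falls in month c + k − 1.

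| Clearance month | Visits up to month 12 (13 − c) | Month of visit 5 | Month of visit 6 | Month of visit 12 (c + 11) |
|---|---|---|---|---|
| 4 | 9 | 8 | 9 | 15 |
| 5 | 8 | 9 | 10 | 16 |
| 6 | 7 | 10 | 11 | 17 |
| 7 | 6 | 11 | 12 | 18 |
| 8 | 5 | 12 | 13 | 19 |

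- DJST time points after month 12 are therefore foreseen: the 12-measurement cap is reached only at months 15 to 19.
- Time-based structure: from month 13 on, only participants without an RTS decision are measured.
- Function-based structure: visits 1 to 5 lie within month 12 for every clearance month from 4 to 8. At visit 6 only month-8 clearers are past month 12. Visits 6 to 9 mix participants who are measured whatever their RTS status with participants who are there only because they have not returned. Visit 10 is past month 12 for all.

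**3. Possible size of the bias.** Assumptions not in the document: half of Classic has returned by the time point; RTS readiness correlates rho = 0.3 to 0.7 with the DJST; pre-post DJST correlation r = 0.5 to 0.8. In SD units, with e1 and e2 independent standard normal:

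- baseline B ~ N(0,1); post value Y = rB + √(1−r²)·e1 + delta·arm
- readiness R = rho·Y + √(1−rho²)·e2 + g·arm; still measured if R < 0
- per arm with mean readiness mu: a = −mu, L = phi(a)/Phi(a), v = 1 − aL − L²
- E[Y] = delta·arm − rho·L; E[B] = −r·rho·L
- var(B) = 1 − (r·rho)²(1−v); cov(B,Y) = r − r·rho²(1−v)
- s is the pooled within-arm slope, weighted by Phi(a); adjusted difference = dE[Y] − s·dE[B]

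Adjusting the gain or the post value for baseline gives the same arm difference, so this matches the planned baseline covariate.

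One case in full (delta 0.3, g 0, rho 0.5, r 0.5):

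- Classic: a = 0, L = 0.798, E[Y] = −0.399, E[B] = −0.199.
- Stop-X: mu = 0.15, L = 0.896, E[Y] = 0.3 − 0.448 = −0.148, E[B] = −0.224.
- dE[Y] = 0.251, dE[B] = −0.0245, s = 0.436.
- Adjusted difference = 0.251 + 0.436 × 0.0245 = 0.262 SD = 3.72 points.

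| rho | Seen difference if true difference is 4.26 (r 0.5 / 0.8) | Loss | Seen difference if true difference is 0 and g = 0.3 (r 0.5 / 0.8) |
|---|---|---|---|
| 0.3 | 4.07 / 4.17 | 4% / 2% | -0.65 / -0.32 |
| 0.5 | 3.72 / 3.98 | 13% / 7% | -1.11 / -0.57 |
| 0.7 | 3.14 / 3.64 | 26% / 15% | -1.63 / -0.90 |

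**4. Comparison with sampling error.** With half remaining, n = 43.5 per group. The baseline-adjusted standard error is 14.2 × √(1−r²) × √(2/43.5): 2.6 points at r = 0.5 and 1.8 at r = 0.8. Each false difference in the table is smaller than one matching standard error.

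**The case against.** **Scope.** A reader might infer that every test using data after month 12, in both structures, compares only participants not yet returned. The schedule does not support that for the function-based structure, where visits 6 to 9 are mixed. A reader might also infer that results up to month 12 are safe in any case. The measurements are, but the model may not be: a complete-case repeated-measures ANCOVA that includes later visits would drop returned participants from all time points. How missing visits are handled is commonly left to a fuller plan, so its absence from a condensed article is not a fault. The absence of a cut-off is different, because the article itself states both the stopping rule and the open-ended set of time points.

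**Link to RTS.** The text tying knee control to RTS is mostly background. In this trial the RTS decision is a shared consensus, it is listed as a separate event from the DJST criterion, and nothing says the blinded ratings reach the deciding clinicians. This stands as a reason to treat the strength of the link as unknown. It does not make a link implausible.

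**Power.** It is tempting to say that power falls from 50% at month 12 to 28% at month 15 (87 against 43.5 per group). Those figures leave out the baseline adjustment that the bias figures use. With effective d = 0.3/√(1−r²), that is 0.346 at r = 0.5 and 0.50 at r = 0.8, power is about 62% to 91% at month 12 and 36% to 64% at month 15. Later comparisons do have fewer participants, but the 50%-to-28% contrast does not describe the planned model.

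**Remedy.** Cutting both structures at month 12 would leave only early clearers at function-based visits 6 to 9, and clearance is itself function-based. This objection is right, and the fix below allows for it.

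**Conclusion.** The point holds within these limits. With no end to the confirmatory time points, the plan as written includes between-arm DJST comparisons that are conditioned on not yet having returned to sport: fully in the time-based structure after month 12, and partially from visit 6 in the function-based structure. The baseline covariate removes some of this selection but not all.

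The direction follows from the design if better knee control favours RTS. The size does not follow from the documents. The 2% to 26% attenuation and the false difference of about -0.3 to -1.6 points rest on assumed correlations and an assumed half of Classic returned. At the lower correlations the bias is small, and it is modest against sampling error throughout. The documents therefore do not support calling the primary result invalid, or attaching one figure to its bias. The change is still worth making: it costs little, and the affected comparisons belong to the confirmatory analysis.

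**What to change.** In Statistical analysis, state that the confirmatory between-arm DJST model includes only:

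- **time-based structure:** time points up to month 12 post surgery;
- **function-based structure:** the first five post-clearance measurements, all of which fall within month 12 for clearance at months 4 to 8.

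Later visits are left out of that model altogether, so that incomplete later data cannot remove returned participants from earlier time points. DJST values after these limits are reported descriptively by arm, with the number still measured and without a between-arm test.

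The assessment schedule stays as it is, and no extra visits, videos or ratings are needed. The cost is that there is no confirmatory DJST comparison after month 12, or after the fifth visit in the function-based structure. Early clearers' visits 6 to 9, although measured regardless of RTS, also leave the function-based test. Clearance at months 4 to 8 is an aim; for anyone cleared later, the fifth measurement would fall after month 12, and the number of such participants should be reported.

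### The repeated-measures ANCOVA for DJST names no common visit window, although visits start at clearance and functional testing stops at return to sport

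*Protocol article*

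**What the plan says.** Under Statistical analysis, DJST is the confirmatory outcome. The article states that "gain-score analyses are performed for differences from pre (baseline) to post (each following time point"). The model named for this is a repeated-measures one, applied to the gain scores "of all outcomes using repeated-measures analyses of co-variance (rmANCOVAs) with potential confounders as co-variates"; baseline values are listed among those covariates. This is done on two data structures. In the time-based one, "statistics are performed on all outcomes assessed at the same real-time after reconstruction". In the functional-based one, the first measurement is the one taken "at the time of being cleared for the assessment (varying times of 4–8 months post reconstruction"). No common window and no primary time point are named.

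The schedule is in the Study flow text after the Fig. 1 caption: "until the unrestricted RTS decision, but at least until 12 months post surgery, all outcomes are assessed once a month". On what follows the RTS decision it says: "After this time point, the participants may continue the intervention but no further functional assessments will be conducted". On the count: "Thus, each participant is measured at least five times to a maximum of 12 times". RTS is aimed at months 12-18. The 18- and 24-month contacts are described as structured telephone interviews, which give no DJST value.

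Statistical analysis also lists the time of the unrestricted RTS decision as a survival event. Reaching more than 60% on the DJST is listed as a separate, functional RTS event.

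**The concern.** A classical repeated-measures ANCOVA works on a rectangular table in which each participant has a value at every visit in the model. This schedule does not produce such a table. Entry is staggered by clearance, and after month 12 exit is governed by the RTS decision. Two things follow.

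- **Lost participants.** With every following time point in the model, participants cleared later lack the early months of the time-based structure, and those who return early lack the late visits of either structure. A complete-case fit would drop them through no fault of conduct.
- **Selected comparison.** After month 12 only participants who have not returned to sport are tested. RTS is an outcome that Stop-X is meant to influence, so the arms are then compared within a group formed after randomisation. Retaining incomplete profiles does not by itself settle what such a comparison estimates.

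This is the trial's only confirmatory analysis, and Sample size determination sets beta at 50%, so planned power is 50% with nothing in reserve.

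**Working it through.** **1. The plan's own figure.** Inputs from Sample size determination: d = 0.3, two-sided alpha 5%, beta 50%, SD 14.2, 30% dropout. A two-sample t-test needs 86.3, so 87 per group, 174 in all; power with 87 per group is 50.3%. Dropout: 174 / (1 - 0.30) = 248.6, so 249, against 250 stated. The figures reproduce.

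**2. Visits per participant.** With monthly visits, the count is RTS month - clearance month + 1.

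- Clearance 8, RTS 12: 12 - 8 + 1 = 5
- Clearance 4, RTS 12: 12 - 4 + 1 = 9
- Clearance 4, RTS 15: 15 - 4 + 1 = 12
- Clearance 4, RTS 18: 18 - 4 + 1 = 15

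The lower bound of five matches the protocol. The stated maximum of 12 is below what the aimed timings can give.

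**3. Complete profiles by design alone.** Assumption, not in the document: clearance is spread evenly over the five months 4-8 and RTS evenly over the seven months 12-18, independently. That gives 35 equally likely pairs. The ranges come from nine combinations of even, early-weighted and late-weighted timing.

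| Window | Share complete | Of 174 | Range |
|---|---|---|---|
| Months 8-12 | 35/35 | 174 | 174 |
| Months 6-12 | 3/5 | 104 | 70-139 |
| Months 4-12 | 1/5 | 35 | 12-58 |
| Months 4-18 | 1/5 × 1/7 = 1/35 | 5 | 0-14 |
| Visits 1-5 | 35/35 | 174 | 174 |
| Visits 1-7 | 32/35 | 159 | 135-172 |
| Visits 1-9 | 25/35 | 124 | 77-160 |
| Visits 1-12 | (4+3+2+1+0)/35 = 10/35 | 50 | 14-97 |

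For visits 1-12, RTS must come at least 11 months after clearance. That leaves 4, 3, 2, 1 and 0 of the seven RTS months for clearance at months 4, 5, 6, 7 and 8.

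**4. Power at d = 0.3** (two-sample t approximation at one time point). With 87 per arm it is 50%; with 17 per arm (months 4-12), 13.6%; with 25 per arm (visits 1-12), 18.0%.

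**5. Who is still tested after month 12.** Under even RTS times, 4/7 = 57% are still under functional assessment at month 15 (range 36-79%) and 1/7 = 14% at month 18 (range 4-25%).

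**6. Selection, as scenarios only.** The true difference is 0.3 × 14.2 = 4.26 points.

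- *Scenario A:* the least-recovered half is still tested, and DJST correlates with RTS readiness at an assumed value. At correlation 0 the observed difference stays at 0.30 SD. At 0.3, 0.5 and 0.8 it becomes 0.28, 0.25 and 0.18 SD.
- *Scenario B:* means 62.14 and 66.4, between-visit correlation 0.6-0.8, and RTS at month 12 whenever DJST exceeds 60%. The month-15 difference among those still tested is 1.9-2.5 points. Decision noise of SD 10 gives 2.7-3.1, SD 20 gives 3.5-3.7, and SD 30 gives 3.8-4.0.

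**The case against.** The article mentions neither listwise deletion nor an SPSS procedure nor a missing-data rule, and an article may leave these to an analysis plan that is not shown. The gain-score wording could also mean one comparison per time point, which needs no complete profile; the reference to post-hoc analyses after significant omnibus testing weakens that reading but does not exclude it. The functional-based structure removes the staggered start. All this stands, so the losses above are conditional on a complete-case model over the full grid.

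A reader might infer that most randomised participants will fall out of the DJST analysis. The documents do not support that as a flat statement: months 8-12 and visits 1-5 keep everyone by design, and visits 1-9 keep 124 of 174 under even timing. Even on visits 1-12, one of the nine timing patterns keeps a majority (97 of 174).

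A reader might also infer that the late comparison is biased against Stop-X by a known amount. It is not. The article keeps the RTS decision and the DJST threshold as two separate events and describes the decision as shared and consensus-based. The attenuation shrinks toward nothing as the decision depends less on DJST. RTS-driven loss also begins only after month 12, because everyone is assessed at least until then.

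Finally, months 4-8 and 12-18 are aims, not limits, and 12 may be a deliberate cap. The visit-count discrepancy is therefore only a clarification.

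What survives is the mismatch itself: the stated model and the stated schedule do not fit together, a workable window exists, and the article does not choose it.

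**Conclusion.** The point holds in a bounded form. The confirmatory DJST method covers every following time point on a schedule whose start and, after month 12, whose end differ between participants by design.

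Under complete-case fitting and evenly spread timings, the full grid would keep about 35 of 174 participants (months 4-12) or 50 of 174 (visits 1-12), and power would fall from 50% to roughly 14-18%. On the shared windows nothing is lost by design. The power figures are for a single-time-point t-test, not for the covariate-adjusted repeated-measures model.

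Comparisons after month 12 are conditional on not having returned to sport. That follows from the schedule and needs no assumption about timing. Its effect on the estimate depends on how strongly DJST drives the RTS decision, which the document does not quantify.

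**What to change.** - Analyse DJST with a linear mixed model for repeated measures, available in the SPSS software already named. Use all post-baseline visits through month 12 of all randomised participants, with visit as a category, arm × visit, and baseline DJST as a covariate.
- Fix the baseline as the first measurement at clearance. Pre-operative values exist only for some participants, and month-4 values only for those cleared by then.
- Take the arm difference at 12 months post surgery, the last visit scheduled for everyone, as the single primary contrast.
- Label DJST comparisons after month 12 as exploratory and conditional on no RTS.
- Separately, reconcile the maximum of 12 measurements with the aimed timings, or state that it is a cap.

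Naming months 8-12 or visits 1-5 as the window would also remove the design-driven gaps while keeping the ANCOVA, but ordinary missed visits would still delete whole profiles in a complete-case fit. The cost of the change is plan wording and different model syntax. No extra data are needed; what is given up is any confirmatory claim after month 12.
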